#### Primary Measure—Quantitative

The primary outcome is the quality of values-clarification processes during simulated treatment decision encounters for advanced cancer, assessed using VECTORS to compare intervention (VOICE) and control (ACS) groups, as well as VB and NVB encounters.

Two independent raters will review the recorded simulations and use VECTORS to estimate the quality of values-clarification observed during each encounter. Rater 1 will assist with recordings; therefore, it will not be blinded. Rater 2 will be blinded, as the recorded simulations will not indicate whether simulations were VB or NVB, or whether participants were in the intervention or control groups. We will calculate the Cohen κ coefficient to evaluate interrater reliability. We will conduct a sensitivity analysis by performing data analysis on the dataset that includes ratings from rater 1, then perform the same data analysis using the dataset that includes ratings from rater 2. We will compare the data analysis results to look for differences.

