## Methods

### Prior Work

We previously developed the Values and Outcomes to Improve Cancer Experiences (VOICE) tool, a digital values-clarification instrument intended to support SDM in oncology settings. To inform the development of VOICE, we conducted a stakeholder-driven concept mapping study involving 7 older adults with advanced cancer, 2 caregivers, and 12 oncology specialists [30,31]. VOICE uses best-worst scaling (BWS) to elicit and prioritize treatment values (ie, what patients value most when making treatment decisions). VOICE also generates a tailored summary report that includes question prompt lists aligned with each patient’s top-ranked treatment values [30,31]. The tailored summary report was designed to prompt patients to discuss their values, ask questions, and express in their own words how the treatment options may affect what matters most to them.

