**Figure 1 figure1:**
[figure not shown]
Randomized pilot testing study schema. (A) Participants will complete informed consent in REDCap (Research Electronic Data Capture) and participant characteristics in Qualtrics remotely before scheduling to engage in simulations. (B) To ensure balanced participation across the 4 potential pathways, a systematic alternating method in Qualtrics will be used to assign participants to the intervention (VOICE) or control (ACS) groups. (C) After participants complete and review VOICE or the ACS guide, they are prompted to contact the research team to schedule the patient-clinician simulated encounters. Patients are reminded they are preparing for a simulated patient-clinician encounter in which they will be asked to discuss and make a decision regarding a “mock” secondary cancer diagnosis. (D) The order of encounter type (VB vs NVB) will be random using a random number generator in Microsoft Excel. (E) All participants will engage in two (20- to 30-minute) simulated encounters (VB and NVB) in random order, both occurring on the same day. Clinicians (ie, medical students portraying oncologists) will only be blinded as to whether the participants received VOICE or the ACS guide prior to the interaction. Clinicians will be informed of the encounter type to ensure they follow appropriate scripts. Simulated encounters will be held at a single site in the Simulation, Experiential Learning, and Training (SET) Center located at the University of North Carolina at Chapel Hill School of Medicine. Simulated patient-clinician encounters will be audio-video recorded. (F) Participants will complete surveys (CollaboRATE and PrepDM [Preparation for Decision-Making]) and engage in semistructured interviews immediately following each simulation. Our research team will complete observed ratings of encounters (VECTORS and OPTION-5) after simulations have concluded by reviewing the audio-recorded simulations. ACS: American Cancer Society; VECTORS: Values Elicitation and Clarification of Treatment Options Rating Scale; VOICE: Values and Outcomes to Improve Cancer Experiences.

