#### Values-Based Simulation Script

A review of literature was performed to assess the best practices in communication and SDM during clinical encounters [21,32-37]. The resulting VB script was designed to model a “high-quality” encounter in which clinicians focus on discussing and incorporating patients’ values into treatment decisions. The quality of the encounter was structured using three levels of situational awareness [38], modified for clinician and patient engagement.

**Level 1—Gathering Information:** Identifying what matters most to the patient when making a treatment decision.**Level 2—Processing Information:** Exploring how the patient’s values are impacted by treatment options.**Level 3—Projecting Information:** Anticipating what will occur after making a decision based on that information.

This script was developed to ensure the oncologist addressed all 3 levels during the encounter, supporting a values-aligned decision-making process.

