Performance actions of participants will be assessed after encounters, including (1) whether participants brought either the tailored digital summary report from VOICE or the ACS guide to the encounter and (2) whether participants informed the clinician they completed and reviewed VOICE or the ACS guide.

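### Rater 2's blinding to arm cannot be assured, because a participant who names VOICE or the ACS guide reveals the arm on the recording; ratings are also not blind to script

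*Protocol article*

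**What the plan says.** Under Primary Measure—Quantitative, two raters score each recorded encounter with VECTORS. On the first, the protocol says "Rater 1 will assist with recordings; therefore, it will not be blinded". The second is described as blinded on the ground that "the recorded simulations will not indicate whether simulations were VB or NVB, or whether participants were in the intervention or control groups". Secondary Measures—Quantitative applies the same two-rater arrangement to OPTION-5.

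Other parts of the article bear on that ground:

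- **Naming the tool.** Secondary Measures—Quantitative lists as a performance action "whether participants informed the clinician they completed and reviewed VOICE or the ACS guide". Secondary Outcome—Quantitative plans to report how many did so.
- **Bringing the tool.** The same section records "whether participants brought either the tailored digital summary report from VOICE or the ACS guide to the encounter".
- **Purpose of the VOICE report.** Prior Work says "The tailored summary report was designed to prompt patients to discuss their values, ask questions".
- **Medium.** The Figure 1 legend says "Simulated patient-clinician encounters will be audio-video recorded" at step E. At step F it says that the team completes VECTORS and OPTION-5 "by reviewing the audio-recorded simulations".
- **Values-based (VB) script.** "This script was developed to ensure the oncologist addressed all 3 levels during the encounter".
- **Nonvalues-based (NVB) script.** The clinician keeps off those levels unless the patient raises values.

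**The concern.** VECTORS and OPTION-5 are judgements made by an observer. Each VECTORS item has only three possible scores (0, 5, 10), so a small change in generosity can move a whole category. A rater who knows that the participant had VOICE may score engagement more favourably.

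Rater 1 is openly unblinded, so rater 2 is the only protection against this for the primary outcome and for OPTION-5. The planned sensitivity analysis runs the same models on each rater's scores and compares the results. A reader will take that as unblinded against blinded. In any encounter where the arm is spoken aloud, both raters know it, and their agreement says nothing about expectation bias.

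The pilot is meant to inform the power calculation of a larger study (Sample Size and Power), so an inflated VOICE versus ACS difference would carry forward.

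**Working it through.** The point turns on setting the sections side by side. Arithmetic only gives the scale.

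**1. Arm.** The stated ground is that the recording does not indicate the arm. Telling the clinician about VOICE or the ACS guide is speech within the encounter, and the encounter is what is recorded and scored. In every encounter where it happens, the recording does indicate the arm. The plan treats this as possible enough to count, and the VOICE report is built to shape what the patient says.

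**2. Carrying the tool.** Whether this reveals the arm depends on the medium. On video, a visible report or guide can do so. On audio, one carried in silently cannot. The Figure 1 legend mentions both audio-video recording and review of audio, so the two need to be reconciled.

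**3. Script.** The VB script takes the clinician through levels 1 to 3, and the NVB script withholds them unless the patient prompts. The three VECTORS clinician-engagement items are those same levels, and the scale was built on the same framework as the scripts. Scoring the clinician items therefore often means recognising the script. Recognition is not certain, because an NVB encounter in which the patient raises values can resemble a VB one.

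**4. Stated safeguards.** Keeping the blinded rater out of interview coding (Secondary Outcome—Qualitative) and repeating the analysis by rater (Primary Measure—Quantitative) both leave the cues on the recording.

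**5. Scale of the risk.** Inputs from the article:

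- The planned sample reproduces: 11 per pathway × 4 pathways = 44. With two encounters each, 44 × 2 = 88 recordings.
- VECTORS has 7 items scored 0, 5 or 10. The raw total of 0-70 is rescaled to 0-100.

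One item moved one category: 5 / 70 × 100 = 7.14 points.

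Let *p* be the share of VOICE encounters in which the tool is disclosed. The article does not give *p*, so the whole range is shown. Assume that each disclosed VOICE encounter gains one category on one item and that ACS scores are unaffected. The spurious arm difference is then *p* × 7.14:

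| *p* | inflation (points, 0-100 scale) |
|---|---|
| 0 | 0 |
| 0.25 | 1.8 |
| 0.50 | 3.6 |
| 0.75 | 5.4 |
| 1.00 | 7.1 |

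The article gives no standard deviation for VECTORS, so I do not convert these shifts into an error rate.

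**The case against.** The other side has several fair points.

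- **The blind has not failed everywhere.** A reader might infer that rater 2's blind to arm cannot hold at all. The text does not support that. The plan records whether participants mention the tool and gives no expected frequency. Where nobody names it, nothing shown reveals the arm directly. This stands, and the claim here is limited to it.
- **Audio review is already written.** Step F of the Figure 1 legend says so, and on audio a silently carried report discloses nothing. This stands. What remains is to reconcile it with step E. Audio hides neither a spoken mention nor the script.
- **Script recognition is built into the design.** The script is the manipulated condition and VECTORS measures what it manipulates. Every participant has both encounter types, so recognising the script does not by itself bias VOICE against ACS. This stands. It calls for an accurate statement rather than a masking step.
- **A condensed article may leave recording handling to the full protocol, and the sentence may only mean that files carry no label.** A missing masking procedure would indeed be no finding. But the article makes a positive statement about what the recordings reveal, and its own text contradicts that statement. If only unlabelled files were meant, the sentence claims too much.
- **The size rests on assumption, and Table 1 anchors each category with criteria and examples.** Both are true. The anchors limit discretion without removing it, and the figures above give scale only.

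**Conclusion.** The concern holds in a limited form. The stated ground for rater 2's blinding is contradicted by the article. Blinding to arm cannot be assured, because it is lost wherever the participant names the tool. Ratings are not reliably blind to VB versus NVB, because the script shows in the behaviour being scored. In disclosed encounters, agreement between raters 1 and 2 is not evidence against expectation bias. The avoidable risk lies in the VOICE versus ACS comparison, for both VECTORS and OPTION-5.

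On VECTORS, the inflation would be between 0 and 7.1 points on the 0-100 scale. This assumes one item moved one category in each disclosed VOICE encounter, no shift in the ACS arm, and a disclosure share anywhere from 0 to 100%. The documents give no evidence of how often disclosure occurred or that either rater's scores were in fact biased.

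**What to change.** 1. Reconcile the two statements on the recording medium in the Figure 1 legend, and confirm that rater 2 scores from audio.
2. Before rater 2 scores, have rater 1, who is already unblinded and assists with recordings, mask only the spoken name of the tool (VOICE or ACS guide). Leave the patient's values statements and questions intact, including any read from the report. They are scored behaviour, and removing them could lower VOICE scores selectively.
3. Have rater 2 record a guess of the arm after each score, and report its accuracy. If VOICE changes behaviour, some correct guessing may reflect a real effect, so read the result with that in mind.
4. Replace the blinding sentence with a statement that rater 2 is not told the allocation and hears audio with tool names masked, and that ratings are not blind to VB versus NVB because script content identifies the encounter.

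The Results section says that the study has been conducted and is ready for analysis, but not whether rating is finished. If it is, make change 4, worded for what was actually done, and report by arm how many encounters disclosed the tool, using the performance-action data. Treat any comparison of disclosed with undisclosed encounters as descriptive only, because disclosure happens after randomisation and is likely to be related to engagement.

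The cost is small: existing staff edit at most 88 recordings, and one field is added per rating. The drawback is that a short masked gap may hint that a tool was mentioned.

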#### Secondary Measures—Quantitative

Data from secondary measures will either be collected through observed ratings by study team members (VECTORS and OPTION-5), participant surveys (CollaboRATE and PrepDM), or interviews, as described below and depicted in Figure 1.

SDM communication behaviors will be subjectively assessed using the OPTION-5 scale [36,37]. OPTION-5 is a validated scale used to assess the extent to which SDM communication behaviors occur during an initial diagnosis encounter. OPTION-5 is a 5-item validated survey that has been used to measure the extent to which clinicians involve patients in treatment decisions, including oncology patients, and is therefore an appropriate assessment for this study [37,41-44]. Five aspects of the clinicians’ behavior during the simulated encounters will be evaluated and rated using a 5-point Likert scale, ranging from “0=no effort observed” to “4=exemplary effort is observed” [37]. The five aspects include the extent to which the clinician (1) draws attention to or confirms alternate treatment options exist, (2) supports the patient to become informed or deliberate about treatment options, (3) gives information or checks understanding about the options available, (4) elicits the patients’ preferences about the options available, and (5) makes an effort to integrate the patients' preferences into the treatment decision [36,37]. Two independent raters will use the OPTION-5 scale to assess the level of SDM observed during each simulated patient-clinician encounter, as described for VECTORS. Interrater reliability and sensitivity analyses will be performed, as described for VECTORS.

The level of SDM that occurs in the simulated encounters from the patient’s perspective will be subjectively assessed immediately following simulations using the 3-item validated CollaboRATE scale [35]. CollaboRATE is a patient-reported assessment that measures patients’ perceived effort of clinicians to (1) understand patients’ health issues, (2) listen to what matters most about their health issues, and (3) include what matters most when choosing a treatment [35].

Usefulness in preparing participants to engage in SDM will be measured immediately following the final simulation using the PrepDM scale. PrepDM scale [45], a validated 10-item scale, will be used to assess participants’ perceived usefulness of the tool in preparing them to communicate with oncologists during the simulated encounter.

Performance actions of participants will be assessed after encounters, including (1) whether participants brought either the tailored digital summary report from VOICE or the ACS guide to the encounter and (2) whether participants informed the clinician they completed and reviewed VOICE or the ACS guide.

#### Secondary Measures—Qualitative

All participants will engage in 2 semistructured interviews immediately following each simulation to assess (1) situational awareness (ie, ability to gather, process, and project information) [38] during the simulated encounter and (2) perceptions of whether VOICE or the ACS guide prepared them for the encounter. Qualitative data from postsimulation interviews will be summarized and grouped into themes, which will be used to understand the impacts of using VOICE or the ACS guide prior to an encounter.

### Data Analysis

Quantitative analyses will be performed in RStudio, and qualitative analyses will be performed in MAXQDA.

#### Sample Size and Power

This pilot study was not powered, as its primary objective was to gather preliminary data necessary to inform the design and power calculations of a future, larger-scale study. We aimed to estimate the quality of values-clarification processes during simulated encounters (as measured by VECTORS, ranging from 0 to 100) for intervention and control groups in 2 different simulated encounters (VB and NVB). We will attempt to enroll 11 participants in each pathway to gather preliminary data, for a total of 44 participants.

The preliminary data gathered from this pilot study, as well as other study outcome measures, will inform future work using VECTORS in real-world and simulated encounters.

#### Participant Characteristics

Descriptive statistics will be used to summarize participants’ demographic characteristics, comfort level with technology, personality (BFI-2-XS [Big Five Inventory-2 Extra-Short Form]) [46], self-reflection and insight (SRIS) [39,47], and preferred role in PSDM [40].

#### Primary Outcome—Quantitative

Simulated encounters will be quantified using VECTORS to assess the estimated quality of values-clarification processes that occur between intervention and control groups during both VB and NVB encounters. Interrater reliability for VECTORS will be assessed by calculating the Cohen κ weighted coefficient and discrepancies in ratings. Kappa statistics between 0.61 and 0.80 indicate substantial agreement between raters, and 0.81 to 1.00 indicate almost perfect agreement between raters [48]. Analyses of the 3 domains in VECTORS include the raw scores (rapport building: 0-10; clinician engagement: 0-30; patient engagement: 0-30). Analyses of VECTORS overall scores involve taking the sum of all 3 domains, producing a raw score of 0-70, then rescaling to a score of 0-100.

Descriptive statistics will be used to report the mean and SD for VECTORS overall and by each domain. Mean and SD will be reported as cross-tabulations for all encounters, and by intervention and control for VB and NVB encounters, and for whether clinicians transitioned from NVB to VB encounters due to patient agency (ie, patients initiated a discussion pertaining to their values).

Linear regression models using generalized estimating equation methods will be fit using all patient data from both encounter types (VB vs NVB) to account for repeated measures per patient. These models will objectively estimate differences by group and by encounter type and test for potential interactions to show if the intervention works better in one scenario compared to the other.

#### Secondary Outcome—Quantitative

Simulated encounters will be subjectively analyzed using the OPTION-5 instrument to assess the extent to which SDM communication behaviors occurred during the simulation. The OPTION-5 scores from each simulation will be summed, producing a score from 0 to 20, then rescaled to a scale of 0-100. Interrater reliability for OPTION-5 will be assessed as described in the primary outcome for VECTORS.

Patient self-reported scores from the CollaboRATE assessment will be summed, then rescaled to a scale of 0-100. CollaboRATE scores will also be dichotomized (perfect score vs nonperfect score) to allow the use of logistic regression. CollaboRATE often shows ceiling effects; therefore, dichotomizing responses improves the variation among participant scores [49,50].

The PrepDM total mean scores will be quantified by averaging 10 subscales. Items will be summed, then divided by 10 to provide a mean score. Scores will be rescaled to a 0-100 scale by subtracting 1 from the summed score and multiplying by 25, with higher scores representing higher perceived levels of preparation in decision-making [45].

Descriptive statistics will be used to report the mean and SD by intervention and control groups for secondary outcome measures: OPTION-5, CollaboRATE, and PrepDM. Mean and SD will also be reported by VB and NVB encounters for OPTION-5 and CollaboRATE, and by whether participants brought the tool (VOICE or ACS guide) for PrepDM scores.

Descriptive statistics will also be used to summarize the number of participants who (1) brought either the tailored digital summary report from VOICE or the ACS guide to the encounter or (2) informed the clinician they completed and reviewed VOICE or the ACS guide.

Kruskal-Wallis tests will be performed to objectively evaluate differences in distributions in OPTION-5, CollaboRATE, and PrepDM scores.

Linear regression models will be performed for OPTION-5, as described in the primary measure for VECTORS. Log-binomial regression models will be performed with all binary patient data from both types (VB vs NVB) to account for repeated measures per patient. These models will objectively estimate differences by group and by encounter type and test for potential interactions to show if the intervention works better in one scenario compared to the other.

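### The PrepDM rescaling rule names the summed score, but it gives the stated 0-100 range only when applied to the item mean

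*Protocol article*

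**What the plan says.** All the relevant text is in the Protocol article. Under Data Collection, Secondary Measures—Quantitative, PrepDM is described as "a validated 10-item scale, will be used to assess participants’ perceived usefulness of the tool", completed after the final simulation. The response options of the items are not given.

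Under Data Analysis, Secondary Outcome—Quantitative, scoring is set out in three consecutive sentences:

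- The first names the quantity to be reported, an average over what it calls 10 subscales.
- The second explains how that average is obtained: "Items will be summed, then divided by 10 to provide a mean score".
- The third gives the rescaling rule, and here the input changes from the mean to the sum: "Scores will be rescaled to a 0-100 scale by subtracting 1 from the summed score and multiplying by 25".

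The same section commits to reporting the PrepDM mean and SD by randomised group and by whether the participant brought the tool. It names Kruskal-Wallis tests for comparing distributions. No regression model is named specifically for PrepDM.

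**The concern.** The second sentence produces a mean, and the third applies the rescaling to the sum. The constants in the third sentence suit a quantity on a 1 to 5 scale, which a sum of 10 items is not. An analyst who codes the rule literally gets scores outside the range that the same sentence promises.

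What is at stake is the descriptive reporting of PrepDM: its means, its SDs and any difference between VOICE and the ACS guide in scale points. PrepDM is the only quantitative self-report measure of preparedness, which is part of the first secondary research question. The section Sample Size and Power says that the VECTORS data and the other outcome measures will inform future work, so the raw figures may be reused. The Results section says that the data are ready for analysis, so the rule should be corrected before scoring.

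**Working it through.** **Inputs**

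- Number of items: 10 (Secondary Measures—Quantitative).
- Sum S, and mean M = S/10 (Secondary Outcome—Quantitative).
- Rule as written: (S − 1) × 25, with a stated result of 0-100 (same section).
- Item coding: not stated. Assumed 1 to 5, for the reason in step 1.

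**Step 1. What the constants require.** Setting (x − 1) × 25 = 0 gives x = 1. Setting (x − 1) × 25 = 100 gives x = 5. The quantity entered must therefore run from 1 to 5, which is the range of the mean of items coded 1 to 5.

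**Step 2. Reproducing the stated range from the mean.** (1 − 1) × 25 = 0 and (5 − 1) × 25 = 100. The stated 0-100 is reproduced exactly.

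**Step 3. The rule as written, from the sum.** S runs from 10 × 1 = 10 to 10 × 5 = 50.

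- Minimum: (10 − 1) × 25 = 225
- Maximum: (50 − 1) × 25 = 1225

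The stated range is not reproduced. Subtracting 1 from the sum and dividing by 10 afterwards does not help either: (10 − 1)/10 × 25 = 22.5 and (50 − 1)/10 × 25 = 122.5.

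**Step 4. Dependence on the assumed coding.** Applying the rule as written to the sum under other codings:

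| Item coding | Range of sum | (S − 1) × 25 |
|---|---|---|
| 1 to 5 | 10 to 50 | 225 to 1225 |
| 0 to 4 | 0 to 40 | −25 to 975 |
| 0 to 5 | 0 to 50 | −25 to 1225 |
| 1 to 4 | 10 to 40 | 225 to 975 |
| 1 to 7 | 10 to 70 | 225 to 1725 |
| 0 to 10 | 0 to 100 | −25 to 2475 |

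None gives 0-100. More generally, with integer item scores the sum of 10 items spans at least 10 points, so the rescaled score spans at least 10 × 25 = 250, which is wider than 100. The mismatch holds for any integer coding. Only the figures 225 and 1225 depend on the 1 to 5 assumption.

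**Step 5. Size of the error in reported figures.** The correct score is C = (S/10 − 1) × 25 = 2.5S − 25. The score as written is W = (S − 1) × 25 = 25S − 25. Since 10C + 225 = 25S − 250 + 225 = 25S − 25, we have W = 10C + 225. It follows that:

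- a mean is 10 times the correct mean plus 225;
- an SD, or a raw difference between groups, is 10 times too large, because the constant 225 drops out.

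As an illustration, a participant with an item mean of 3 has S = 30. The correct score is (3 − 1) × 25 = 50, and the rule as written gives (30 − 1) × 25 = 725 = 10 × 50 + 225.

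**Step 6. What does not change.** W is an increasing linear function of C, so ranks are preserved and the Kruskal-Wallis statistic is identical. A standardised difference is also identical, because numerator and denominator both carry the factor 10.

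**The case against.** The strongest reply is that this is one wrong word. The two preceding sentences define the score as a mean, dividing by 10 would serve no purpose if the sum were then rescaled, and the target range is stated in the same sentence. Under 1 to 5 coding the lowest possible score as written is 225, so every value would fall outside the stated range and the slip would show at the first calculation. This stands as an argument about severity. It does not make the written rule correct, and nothing elsewhere in the article corrects it.

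Three stronger readings are tempting, and the article does not support them:

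- A reader might infer that preparedness is measured by PrepDM alone. Secondary Measures—Qualitative says that the interviews also ask whether VOICE or the ACS guide prepared participants, so PrepDM is the only quantitative self-report measure and not the only measure.
- A reader might infer that the comparison of groups, or any effect size carried to a later trial, would be wrong. The only test named for PrepDM is rank-based, and standardised effects are unchanged. A sample size computed from a difference and an SD on the same mis-scaled metric would also be unchanged. Only figures in raw units are affected. Sample Size and Power ties future work mainly to VECTORS and does not name PrepDM as the basis for powering.
- A reader might take 225 to 1225 as a fact of the plan. It rests on an inferred item coding.

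**Conclusion.** The point holds as a minor error that is wrong as written. The scoring rule cannot yield its own stated 0-100 range from the summed score under any integer item coding. It does so exactly when applied to the item mean with items coded 1 to 5. On that coding, the rule as written gives 225 to 1225.

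The consequence is confined to the descriptive means, SDs and raw-unit differences of one secondary outcome in a pilot that was not powered. The primary outcome and the named test for PrepDM are untouched. Correction is still worthwhile because the article is an operative, published scoring instruction that others may copy.

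**What to change.** Replace the scoring text with a single definition: PrepDM 0-100 score = (mean of the 10 items − 1) × 25. When all 10 items are answered this equals (sum − 10) × 2.5, which gives (10 − 10) × 2.5 = 0 and (50 − 10) × 2.5 = 100. State the 1 to 5 item coding alongside it, once confirmed against the form used, so that the formula can be checked from the text. In the same paragraph, refer to 10 items and not 10 subscales, to agree with the description under Secondary Measures—Quantitative; this has no numerical effect.

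The cost is one sentence of text and one line of code, with no change to data collection. A check that every PrepDM score lies between 0 and 100 would confirm that the code follows the corrected rule.

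### The Kruskal-Wallis tests for OPTION-5 and CollaboRATE are not limited to one score per participant, although every participant has two; they do not fit VB vs NVB comparisons or arm comparisons on pooled encounters

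*Protocol article*

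**What the plan says.** The Figure 1 legend sets the structure of the data: "All participants will engage in two (20- to 30-minute) simulated encounters (VB and NVB) in random order". OPTION-5 is rated for each encounter and CollaboRATE is completed after each one. Under Sample Size and Power the article says "We will attempt to enroll 11 participants in each pathway to gather preliminary data, for a total of 44 participants", and also that "This pilot study was not powered".

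Under Secondary Outcome—Quantitative, OPTION-5 and CollaboRATE are to be summarised by arm and also by encounter type. Four statements on tests and models follow in that section:

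- Rank tests: "Kruskal-Wallis tests will be performed to objectively evaluate differences in distributions in OPTION-5, CollaboRATE, and PrepDM scores". No factor, unit or restriction is given.
- OPTION-5 model: "Linear regression models will be performed for OPTION-5, as described in the primary measure for VECTORS". The primary section reads "Linear regression models using generalized estimating equation methods will be fit using all patient data from both encounter types (VB vs NVB".
- Reason for the binary score: "CollaboRATE scores will also be dichotomized (perfect score vs nonperfect score) to allow the use of logistic regression".
- Binary model: "Log-binomial regression models will be performed with all binary patient data from both types (VB vs NVB) to account for repeated measures per patient".

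PrepDM is placed after the final simulation under Secondary Measures—Quantitative. The Figure 1 legend lists it with the surveys completed after each simulation.

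**The concern.** Kruskal-Wallis treats every score as coming from a different person. Here each person supplies two. The authors recognise this for VECTORS and OPTION-5, where they name GEE, but the rank tests carry no such protection and no limit to one score per person.

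The section sets out two contrasts for OPTION-5 and CollaboRATE: between arms and between encounter types. The second always compares the same people with themselves. The first does so, in part, whenever both encounters are pooled. Depending on use, the p-value is too small or too large.

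This matters most for continuous CollaboRATE. The linear model is assigned to OPTION-5 and the log-binomial model to binary data, so the rank test is all that is stated for the continuous version of the patient-reported SDM score, which serves the first secondary research question.

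**Working it through.** **Inputs from the article.** 4 pathways × 11 = 44 participants, which reproduces the stated total. 44 × 2 encounters = 88 scores. With equal arms, that is 22 participants and 44 scores per arm.

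**Inputs assumed.** The article gives no within-participant correlation ρ and no alpha. I take ρ = 0.3, 0.5 and 0.7 and a two-sided 5% level. The 2 SD and 0.5 SD shifts between VB and NVB are also illustrative.

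**Arms, both encounters pooled, equal VB and NVB means.** The test takes the variance of an arm mean as σ²/44; it is σ²(1+ρ)/44. True error = 2[1 − Φ(1.96/√(1+ρ))].
- ρ = 0.3: 1.96/√1.3 = 1.72, error 8.6%
- ρ = 0.5: 1.96/√1.5 = 1.60, error 11.0%
- ρ = 0.7: 1.96/√1.7 = 1.50, error 13.3%

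**Arms, pooled, VB higher by d SD.** The shift cancels between arms, since everyone has one encounter of each type, but it inflates the spread that the test sees to about σ²(1 + d²/4). With d = 2 the variance ratio is (1+ρ)/2, which is below 1, so the test becomes conservative. Simulation of the rank test gives the sizes below.

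**VB vs NVB.** The true variance of the difference is (1−ρ) times what the test assumes. True error = 2[1 − Φ(1.96/√(1−ρ))].
- ρ = 0.3: 1.96/√0.7 = 2.34, error 1.9%
- ρ = 0.5: 1.96/√0.5 = 2.77, error 0.6%
- ρ = 0.7: 1.96/√0.3 = 3.58, error 0.03%

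**Simulation of the tests themselves** (22 per arm, two scores each):

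| Use of the test | ρ = 0.3 | ρ = 0.5 | ρ = 0.7 |
|---|---|---|---|
| Arms, pooled, equal means: error | 8.5% | 10.4% | 13.2% |
| Arms, pooled, VB 2 SD higher: error | 1.1% | 1.8% | 2.5% |
| VB vs NVB: error | 2.2% | 0.7% | 0.1% |
| VB vs NVB, 0.5 SD: Kruskal-Wallis power | 63% | 65% | 69% |
| VB vs NVB, 0.5 SD: signed-rank power | 76% | 88% | 98% |
| Arms within one encounter type: error | 4.9% | 4.7% | 4.9% |

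A separate run of the two power rows gave 64–70% and 76–99%. A four-group test (arm × encounter type) had error of 3.3–4.6% over ρ = 0.2–0.8.

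**Binary CollaboRATE.** If the log-binomial model were fitted with no clustering, the between-arm error would be about 7.6%, 10% and 12% at the three correlations. With a participant-clustered variance it is 3.3–4.3%. On the name of the model: for 60% vs 40% perfect scores (illustrative), the risk ratio is 0.60/0.40 = 1.5 and the odds ratio is (0.60/0.40)/(0.40/0.60) = 2.25.

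**The case against.** The strongest reply is that the article never says the 88 scores are pooled. The primary section cross-tabulates VECTORS by arm within VB and NVB encounters, and the rank tests may be meant the same way. Each participant then contributes one score and the error is about 5%. This stands, so a reader who infers that the planned secondary p-values are wrong goes further than the text allows. What remains is that the text does not say so, and that encounter type is a contrast the section itself sets out, for which no version of this test respects the pairing.

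A reader might also infer that the log-binomial model will ignore clustering. The text does not support that. The sentence states the aim of handling repeated measures, mirrors the primary model sentence and follows the cross-reference to GEE. Including both encounters does not itself achieve that aim, but this is an unnamed method, which a fuller plan may supply. The 7.6–12% error applies only to an analysis that would contradict the stated aim.

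The conflict between logistic and log-binomial is one of wording: the first appears in the reason for dichotomising, the second where the model is specified. PrepDM, if taken once, suits the test.

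Finally, the simulations use roughly normal scores, whereas the article itself notes ceiling effects for CollaboRATE. The direction of the errors does not depend on this; the exact percentages may.

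**Conclusion.** The point holds conditionally. Kruskal-Wallis does not fit two of the comparisons that the wording permits for OPTION-5 and CollaboRATE. For VB vs NVB it is conservative and gives up roughly 10 to 30 points of power at a 0.5 SD difference. For arms on pooled encounters it runs at about 8–13% when the encounter types score alike and about 1–2.5% when VB is 2 SD higher. The scripts are designed to differ in quality, so the direction of error in a pooled test cannot be known beforehand. For arms within one encounter type, and for PrepDM measured once, there is no defect.

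Severity is moderate. Only secondary outcomes are affected, VECTORS and OPTION-5 also have GEE models, and the pilot is unpowered. The sizes rest on an assumed positive correlation of 0.3–0.7, an assumed 5% level and illustrative shifts, because the article states none of these.

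**What to change.** State the factor and unit of each rank test, in one of two ways:

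1. Compare arms within each encounter type (one score per participant) and use a Wilcoxon signed-rank test for VB vs NVB; or
2. Drop the rank tests for OPTION-5 and continuous CollaboRATE, and extend to CollaboRATE the participant-clustered GEE already planned for VECTORS and OPTION-5.

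Minor clarifications to make at the same time:

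- Name GEE clustered on participant for the log-binomial CollaboRATE model. Modified Poisson with robust variance is an option if that model fails to converge, not a requirement.
- Use one model name, logistic or log-binomial, and report the matching effect measure.
- Reconcile the two statements of PrepDM timing. If it was collected after each simulation, say which score is analysed.

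The cost is a few sentences and a few lines of code, with no new data. The article reports the data as ready for analysis, so the choice should be recorded, with its date, before any secondary result is seen.
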